### Sample size

3.4

The sample size for the 3-arm study was determined considering the different decrease of leptin values (an indirect estimate of the primary endpoint leptin sensitivity), following the intervention (mean values of 10 mg/dL in the IHBT group compared to 6 mg/dL in the ST+IHBT or CT+IHBT group, SD = 4). An effect size of 1 was considered as clinically relevant (comparing CT+IHBT group vs. IHBT group and ST+IHBT group vs. IHBT group using Student’s t-test).

Pairwise comparisons will be performed with a significance threshold of p < 0.017 to account for multiple comparisons (3 comparisons), using Bonferroni corrections (p = 0.05/3). To achieve a significance level of alpha equal to 0.017 and a study power of 95%, 30 patients per group are required; considering a 30% dropout rate during follow-up, the plan is to recruit a total of 120 participants (40 per group). Missing data will be excluded from the statistical analyses; otherwise, if the proportion of missing values does not exceed 20%, we will use a mean substitution method, or a multiple imputation method (as for example KNN) as needed.

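### The missing-data rule permits single mean substitution or KNN with the mean unspecified and the choice left open: arm-mean filling inflates type I error, overall-mean filling dilutes the effect

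*Protocol article*

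**What the plan says.** The rule stands at the end of section 3.4 (Sample size) of the protocol article. The default is that "Missing data will be excluded from the statistical analyses". The exception is that "if the proportion of missing values does not exceed 20%, we will use a mean substitution method, or a multiple imputation method", the latter illustrated by "as for example KNN) as needed".

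Three things are not stated: which mean is substituted (the child's arm or the whole sample), what decides between the two imputation options, and whether the 20% is counted per child, per variable or per visit.

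The same section sets a "significance threshold of p < 0.017 to account for multiple comparisons (3 comparisons"), bases the sample size on a comparison "using Student’s t-test", and allows for 30% dropout over follow-up by recruiting 40 per arm.

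**The concern.** This is a stated rule, not a detail left to a later analysis plan, and one method it permits is not valid for inference. Mean substitution adds values that carry no information but counts them as observed. Depending on the mean used, either the standard error is too small or the arms are pulled towards each other.

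KNN ordinarily returns one completed data set. Calling it multiple imputation suggests that imputation uncertainty is carried into the standard error, and in a single fill it is not. Leaving the method to be picked as needed means that it can be picked after the data are seen.

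At stake are the error rate that the Bonferroni threshold in the same section is meant to protect, and the size of the reported effect. At higher missingness the rule falls back on dropping randomised children.

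**Working it through.** **The plan's own figure.** Inputs from section 3.4: "mean values of 10 mg/dL in the IHBT group compared to 6 mg/dL in the ST+IHBT or CT+IHBT group, SD = 4", so the standardised effect is (10 − 6)/4 = 1.0, as stated ("An effect size of 1 was considered as clinically relevant"); alpha 0.017 per comparison; and "study power of 95%, 30 patients per group are required". A t-test power calculation gives 30 per arm with one-sided alpha 0.017 (power 95.3%). Two-sided, it gives 34 per arm, and 30 per arm has 91.8% power. The section does not state sidedness; two-sided tests are used below.

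**Assumptions for the check.** Three arms of 40 (section 3.3), outcome SD 1, equal missingness in each arm, missing completely at random, and three pairwise two-sided t-tests at p < 0.017. The missing-data mechanism is an assumption; the documents give none.

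**Arm-mean filling, 20% missing (32 observed, 8 filled per arm).**
- True SE of a difference: √(2/32) = 0.250.
- Filled values add nothing to the sum of squares, so the reported variance is 31/39 of the observed one. Reported SE: √((2/40) × (31/39)) = 0.199.
- Ratio: √((31/39) × (32/40)) = 0.797, so the SE is about 20% too small.
- Per-comparison error (normal approximation): the two-sided 0.017 critical value is 2.387; 2.387 × 0.797 = 1.903; two-sided tail 0.057. Simulation (100,000 trials) gives 0.056.
- Family-wise error by simulation: 0.135 to 0.137 in repeated runs.

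| Missing | SE ratio | Per-comparison error | Family-wise error, arm mean | Family-wise error, available cases |
|---|---|---|---|---|
| 5% | 0.949 | 0.023 | 0.060 | 0.045 |
| 10% | 0.899 | 0.032 | 0.081 | 0.045 |
| 15% | – | 0.042 | 0.105 | 0.046 |
| 20% | 0.797 | 0.056 | about 0.135 | 0.045 |

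**Overall-mean filling, 20% missing.**
- Each filled arm mean is 0.8 × (observed arm mean) + 0.2 × (overall mean). The overall mean cancels, so the estimated difference is 0.8 × the observed difference: 1.0 becomes 0.80.
- The estimator's SD shrinks too: 0.8 × 0.250 = 0.200, close to the reported SE of 0.199. Family-wise error therefore stays at about 0.045.

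**KNN as a single fill, 20% missing (6,000 trials per setting; k = 1 or 5; assumed covariate correlation 0 to 0.7).**
- Donors from the child's own arm: family-wise error 0.08 to 0.14.
- Donors pooled across arms: 0.039 to 0.046.

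**Exclusion at the planned dropout.** 30% exceeds the 20% ceiling. 40 × 0.70 = 28 per arm, against 30 required. Two-sided power at effect size 1 is 89.5% with 28 per arm and 91.8% with 30.

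**A valid method, 20% missing.** Available cases, valid under the assumed mechanism, stand in here for a likelihood model or proper multiple imputation. They give per-comparison error 0.017, family-wise error 0.045 and power 93.6% at 32 per arm.

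**The case against.** The strongest reply is that the inflation depends on a choice the article does not make. Section 3.4 does not say arm mean. Under the overall mean type I error is preserved, the reported SE matches the estimator's real variability, and the remaining harm is conservative. That is correct, and it limits the claim: a reader might infer that the rule as such nearly triples the family-wise error, but this needs arm-mean filling (or within-arm KNN at its worst) at the 20% ceiling. It does not clear the rule, because a 20% understatement of the effect is also a wrong answer.

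Second, the wording allows multiple imputation in general and gives KNN only as an example. This also stands: a properly executed multiple imputation would comply with the text and would be valid. What remains is a misleading example and an open choice.

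Third, a reader might infer that the plan will always discard its dropouts because 30% exceeds 20%. The documents do not support that. The 30% is dropout during follow-up, which section 3.6 extends to T2, 12 weeks after the intervention; missingness at T1 may be lower. The 20% also has no stated unit. For the same reason the inflated error and the exclusion are alternatives at different levels of missingness, not two faults in one analysis.

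Fourth, exclusion is valid under the mechanism assumed in the calculations, and the article gives no dropout by arm. Unequal dropout is plausible, since social training requires weekly attendance at a site in Rome (section 3.5.4), cognitive training uses the family's own device (section 3.5.3), and section 3.5.2 itself links travel to dropout. But no bias can be put in figures from the documents.

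**Conclusion.** The rule is wrong as written and should be changed. Mean substitution is harmful under either reading: family-wise error of up to about 13.5%, 2.7 times the nominal 5%, if arm means are used at the 20% ceiling; or a 20% dilution of the effect with error near 4.5% if the overall mean is used. Single within-arm KNN lies between 8% and 14% at the same ceiling. At 5% to 10% missing, arm-mean filling gives about 6% to 8%.

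If missingness reaches 30%, the rule leaves 28 per arm, below the plan's own requirement. The analysis is then unbiased only under restrictive assumptions about why children are missing.

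The figures rest on data missing completely at random, equal missingness by arm and two-sided tests. The direction of each fault follows from the method itself and is not in doubt. Which fault would occur cannot be told from the article.

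**What to change.** In section 3.4, delete mean substitution, KNN as a single fill, the 20% switch and the provision that the method is chosen as needed. In their place, prespecify one primary method that includes all randomised children by assigned arm. Either of these would do:

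- a likelihood-based repeated-measures model over T0, T1 and T2, which uses all observed values under missing at random; or
- proper multiple imputation with arm in the imputation model and results combined by Rubin's rules.

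A sensitivity analysis under missing not at random would be a useful addition but is optional.

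The cost is wording. No further data are needed and standard software suffices. Intervals will be wider than under arm-mean substitution (SE 0.250 rather than 0.199 in the 20% example), because that method's intervals are too narrow.

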### Interventions

3.5

All participants of the RESILIENT project will be provided with personalized dietary plan and a PA training as follows:

#### Physical activity training

3.5.2

A kinesiologist ([name]) from the research team will provide participants with PA education to support the engagement in enjoyable and healthy daily activities, aiming to enhance motor competence and confidence. The kinesiologist will develop a structured exercise program tailored to the participant’s initial physical abilities and cardiorespiratory capacity, such as aerobic capacity, flexibility and coordination assessed at baseline. This approach seeks to improve physical fitness, enhance quality of life and support the achievement of age-appropriate physical levels. The PA training will be supervised by the kinesiologist over the 8-week period, with sessions held 2 to 3 times per week, depending on whether the participant practices sports. Each session will begin with a 10-minute warm-up and conclude with a 10-minute cool-down and stretching period, lasting approximately 60 minutes in total (26). The PA training will include weight-bearing and non-weight bearing games, aerobic, proprioceptive and resistance exercises, within a fun and supportive environment. All sessions will be conducted online. The decision to implement remote training is based on several considerations. Firstly, it aims to alleviate the burden and discomfort on the families, who would otherwise have to accompany the participant to a potentially distant gym, thereby reducing the risk of dropout. Moreover, conducting PA training in a gym setting could introduce social influences that may compromise the study’s validity, allowing at the same time the standardization of treatment across all participants. Lastly, during the COVID-19 pandemic, tele-exercise has demonstrated efficacy in managing paediatric obesity, facilitating behavioural changes, and promoting adherence to PA programs (39).

#### Cognitive training

3.5.3

Participants will undergo an 8-week CT+IHBT program, 3 days a week, with each session lasting approximately 25 minutes. The training will be conducted using Cogmed (109), a commercial program that consists of a series of brief exercises that train cognitive functions such as attention and memory. The adaptive nature of the program ensures that the training intensity adjusts to each participant’s performance level, progressively increasing difficulty as they improve. The program’s interface is structured to be appealing and suited for school-age children, with brightly coloured elements. Correct responses are reinforced with positive visual cues (for example, lighter colours), while incorrect responses are signalled with negative ones (for example, darker colours). Additionally, as a reward for completing each training session, participants will be able to build and decorate their own *“island”*. Participants will use their own electronic devices, such as computer or tablet.

### Study assessments

3.6

Outcome variables for all participants will be assessed at baseline (T0), at the end of the 8-week intervention (T1, end of month 2), and 12 weeks after the intervention (T2, end of month 5) to verify the persistence of effects. During the intervention period (T0-T1), participants will receive 3 online nutritional counselling sessions, each conducted every 15 days. Additionally, 2 online follow-up sessions (between T1-T2) are scheduled to occur once per month with nutritionists and PA trainer to support adherence to dietary guidelines, monitor progress, and provide ongoing support.

**Figure 2** provides a detailed overview of the assessment and procedural steps involved in the study protocol across all phases of the research. Further details regarding the specific measures and evaluations conducted at each stage of the study will be extensively described in the subsequent sections of the manuscript.

**Figure 2 f2:**
[figure not shown]
RESILIENT project procedure and assessments. Participants will undergo 3 assessment phases: baseline (T0), post-intervention (T1), and follow-up (T2). Each phase includes 2 days of testing. After the baseline assessment (T0), participants will be randomly assigned to one of 3 treatment groups (IHBT, CT+IHBT or ST+IHBT). All groups will receive nutritional counselling and PA training between T0 and T1. Additionally, one group will undergo cognitive training (CT+IHBT group), while the other group will undergo social training (ST+IHBT group). Monthly follow-ups will be conducted between T1 and T2.

At baseline (T0), all participants will undergo a comprehensive evaluation to collect socio-demographic information, including parents’ education, occupation and socioeconomic status. Data on each participant’s developmental milestones will also be gathered. Participants’ data will be recorded using the electronic health record.

To verify the efficacy of each training program (IHBT, CT+IHBT and ST+IHBT groups) a series of clinical, biochemical, psychological, cognitive and physiological measures will be assessed at each time point (T0, T1 and T2). Biological samples, including plasma, urine, faeces and PBMCs, will be collected and stored in accordance with good clinical practice.

The assessment will take place over 2 days: on the first day, cognitive, psychological, physical, and cardiorespiratory functions will be evaluated. On the second day, blood samples will be collected for haematochemical analysis, and indirect calorimetry will be performed to assess basal energy expenditure and OGTT-induced thermogenesis. Additionally, a comprehensive nutritional evaluation will be conducted.

All anthropometric and biochemical measurements will be conducted after an overnight fast, with participants instructed to avoid consuming any liquids for 4 hours before the analysis and to refrain from engaging in PA on the day prior to testing.

The integration of multiple assessment time points, combined with a randomized study design, will allow for a comprehensive evaluation of both short- and long-term effects of the intervention, enabling a comparative analysis of the different training programs.

#### Physical and physiological assessments

3.6.1

Height will be measured with a Holtain stadiometer, while weight will be recorded using scales certified for medical use (90/384/EEC, SECA, Hamburg, Germany) with patients wearing minimal clothing. The average of 2 measurements will be used. BMI will be calculated using the standard formula: weight (kg)/height (m²), and the BMI z-score will be calculated using CDC reference values, expressed as SD score (37). Additionally, waist, hips and abdominal circumferences will be measured by non-elastic measuring tape. Body composition will be assessed through single-frequency Bioelectrical Impedance Analysis (BIA; DS Medica, BIA Light, Milano).

Indirect Calorimetry (COSMED, Q-NRG) will be conducted under fasting condition (8-hours fasting) for 15 minutes, with participants instructed to remain still, silent and awake during the test. Additionally, indirect calorimetry will be performed during the OGTT for 60 min, starting immediately after the oral glucose challenge (41). Resting Energy Expenditure (REE), Oxygen Consumption (VO2), Carbon Dioxide Production (VCO2), and Respiratory Quotient (RQ) will be recorded. Carbohydrate, lipid and protein oxidation, as well as Diet-Induced Thermogenesis (DIT), will be all estimated (42).

Biochemical analyses will include a complete blood count, blood lipids, liver and thyroid function tests, glucose, insulin and C-peptide, with the latter 3 measured at each OGTT time point using commercial kits.

Plasma samples will also be analysed for circulating levels of adipokines and cytokines (R&D Systems, Inc. [name]), including leptin, Brain-Derived Neurotrophic Factor (BDNF), a key regulator of neural plasticity and appetite suppression (43), Pro-OpioMelanoCortin (POMC) and its derivative Melanocyte-Stimulating Hormone (MSH), which play a central role in the anorectic response to leptin, eotaxin/CCL11, a proinflammatory chemokine linked to age-related cognitive decline (44), and Insulin-like Growth Factor-Binding Protein 2 (IGFBP2), a liver-derived protein regulated by leptin and involved in glucose homeostasis (45), also recognized as a marker of leptin sensitivity during weight loss (46).

Additionally, during the OGTT, acetylated ghrelin, Peptide YY (PYY), and Glucagon-Like Peptide (GLP) will be measured at each time point to further assess hormonal responses to glucose intake.

#### Lifestyle assessment

3.6.2

Examiners will interview parents about their children’s lifestyle habits, including PA, sports participation, and sedentary behaviours, focusing on the frequency and duration of these activities. The assessment will also include detailed questions regarding children’s use of electronic devices, examining the weekly usage duration for each type of device, including television, computer, mobile phone, tablet, and gaming console. **Table 1** provides a brief overview of the tools that will be utilized to assess various lifestyle behaviours, including PA, sleep and eating habits.

**Table 1 T1:** Brief description of tools that will be used to assess lifestyle behaviours including physical activity, sleep and eating habits.

Tool name	Constructs Assessed	Type	Outcome
Children’s Physical Activity Questionnaire (PAQ-C)	Frequency of sports and leisure activities, physical activity performed during the day (physical education classes, recess time, lunchtime, after school activities on weekday evenings and weekends)	Self-report	Raw Scores
International Physical Activity Questionnaire Short form (IPAQ-SF)	Moderate-intensity activities, vigorous-intensity activities, walking and sedentary habits, their frequency and duration on weekday and weekends	Parent-report	Raw Scores
The Sleep Disturbance Scale for Children (SDSC)	Disorders in initiating and maintaining sleep, sleep breathing disorders, arousal disorders, sleep–wake transition disorders, excessive sleepiness, and nocturnal hyperhidrosis	Parent-report	T-Scores
Eating Habits Questionnaire	Eating Habits	Parent-report	Qualitative Scoring
Food Diary	Eating Habits	Self-report	Qualitative Scoring
KIDMED	Adherence to Mediterranean Diet	Parent-report	Raw Scores

Motor and sedentary habits will be assessed using the self-reported Children’s Physical Activity Questionnaire (PAQ-C; 47), which measures moderate-to-vigorous PA levels over the past 7 days. The questionnaire consists of 9 items, rated on a 5-point Likert scale (1 = low activity, 5 = high activity), covering daily contexts. The overall score is calculated as the average of all items, excluding minus the last one, which serves as a qualitative indicator. Higher scores reflect greater levels of PA, while lower scores suggest a more sedentary lifestyle. Although no strict cut-off values are defined, raw scores allow for group comparisons and longitudinal tracking of PA levels.

During 2 online follow-up sessions (between T1-T2), the PA trainer will administer the parent-reported International Physical Activity Questionnaire Short form (IPAQ-SF; 48) for PA monitoring. The raw score will be calculated in MET-minutes/week by multiplying reported time spent in vigorous (8.0 METs), moderate (4.0 METs), and walking (3.3 METs) activities. Total MET-min/week determines 3 PA levels: low (< 600 MET-min/week), moderate (600 – 3.000), and high (> 3.000). Sedentary behaviour is recorded in minutes per day but will not contribute to the total MET score.

To assess sleep habits and quality, the Sleep Disturbance Scale for Children (SDSC; 49) will be employed. This standardized parent-report questionnaire evaluates various aspects of children’s sleep, including duration, onset time, sleep disorders and an overall measure of sleep disturbances in children and adolescents aged 6 to 15 years. Six main areas are investigated by the following subscales: Disorders in Initiating and Maintaining Sleep (DIMS), Sleep Breathing Disorders (SBD), Arousal Disorders (DA), Sleep–Wake Transition Disorders (SWTD), Excessive Sleepiness (DES), and Nocturnal Hyperhidrosis (NH). For each subscale raw scores will be converted in T-scores (M = 50, SD = 10).

Eating habits will be assessed through a combination of parent-report and self-report tools. Parents will complete a home-made eating habits questionnaire, while children will record their daily meals and snacks in a self-reported 7-day Food Diary. Both will be qualitatively analysed to provide insights into the child’s dietary patterns over the week. The evaluation will follow CREA (50) guidelines, including assessments of meal completeness, appropriate daily meal organization (5 meals-per-day), fruit and vegetable consumption (5 portions per day), age-adequate portions, and the frequency of weekly consumption of second courses (for example, meat, fish, legumes, eggs, cheese). Additional factors such as the absence of processed and industrially derived foods, sweets, and sweetened beverages, as well as water intake, will also be investigated. Macronutrient composition and calorie intake will be calculated from the Food Diary for comparisons during and after the intervention.

To assess adherence to the Mediterranean diet, the parent-reported KIDMED questionnaire (51) will be used. This 16-item measure assigns a score of -1, 0 or +1 to each item, resulting in a raw score ranging from 0 to 12 (< 3 = low adherence, 4-7 = medium adherence, > 8 = high adherence), referred to as the *“KIDMED score”*.

Finally, participants will receive in-person nutritional counselling with a nutritionist of the team to explore additional dietary habits and assess the presence of hyperphagia and voracity during meals.

#### Physical and cardiorespiratory assessment

3.6.3

Physical exercise capacity will be assessed through a series of exercises focusing on cardiorespiratory fitness, joint mobility, flexibility, muscle strength, and balance. The aerobic power will be measured using a heart rate monitor, metronome, stopwatch and step counter (52). Joint mobility will be assessed through a Scapular-Humeral Circumduction test, conducted with a calibrated stick, where the result is the last completed circumduction with extended arms. Ankle dorsiflexion will be evaluated using the Knee to Wall test, where participants move their foot back until the knee touches the wall while keeping the heel on the ground. Column mobility will be measured manually with the Fingertip-To-Floor, assessing the distance of the fingers from the ground during forward bending (53).

Flexibility will be assessed using 2 tests: the Sit and Reach test, which measures the distance from the fingertips to the toes during forward trunk flexion, and the Lateral Trunk Flexion test, which records the difference between the initial hand position and the maximum flexion (54).

Muscle strength will be assessed through multiple tests: upper limb strength will be evaluated with a Floor Press test using calibrated dumbbells based on each participant’s strength, while handgrip strength will be assessed using a dynamometer. Lower limb explosive strength will be measured with the Standing Long Jump test, where participants jump as far as possible, landing with both feet together; the best of 2 attempts will be considered (54). Abdominal strength and endurance will be assessed with a Sit-Up test, where participants lie supine with their legs bent at 90° and perform sit-ups, with the result being the maximum number of repetitions performed in 60 seconds (55). Trunk strength will be assessed with a Trunk Lift test, where participants lie prone and lift their upper body to the maximum extent, with the chin-to-floor distance recorded (56).

Lastly, balance will be assessed using the Modified Clinical Test of Sensory Interaction and Balance Variant with drop counting, where participants maintain a single-leg stance within a shoe-sized rectangle for 60 seconds, with the number of falls recorded (57). The decision to utilize tests selected from various fitness test batteries was made to ensure a comprehensive, health-oriented evaluation of physical fitness, while also considering feasibility for both the participants and the setting of the project, while accounting for practical and age-related factors.

